### Randomization and Treatment Allocation

Treatment allocation for this study is depicted in Figure 1. Upon enrollment in the project, individuals with first-episode psychosis will be randomized to either the MFG and CR condition or the MFG alone condition. Randomization will be completed using a block randomization procedure with blocks of varying sizes.

**Figure 1 F1:**
[figure not shown]
Patient Flow Diagram

### Interventions

#### Multifamily Group Psychoeducation

Per the protocol outlined by McFarlane [11], the MFG intervention involves three phases: (i) joining, a process of engaging patients and their key family members, (ii) a psychoeducational workshop, and (iii) multifamily problem-solving sessions. During the joining phase, family members meet with the clinician who will lead the MFG to discuss their ill relative's clinical history, the family's experience and understanding of their ill relative's illness, and family members' concerns and questions with regard to participating in a multifamily group. Concurrent to these sessions with the family, the individual with first-episode psychosis will also complete three individual sessions with the clinician to build rapport and trust in the relationship between the clinician and the individual with first-episode psychosis. Following the completion of the joining phase, family members and clinically stable patients participate in a day-long educational workshop on psychosis which provides an overview of the causes and prognosis of psychotic disorders, current treatments for these disorders, and the ways in which family members may be affected by severe mental illness in the family. Family members are also presented with guidelines for illness management as well as strategies to maintain family balance and well-being. Following the completion of the psychoeducational workshop, families and their ill relatives begin to participate in bi-weekly multifamily problem-solving sessions. During the problem solving sessions, caregivers and ill relatives identify challenges or problems occurring in their lives and identify possible solutions to these problems through a structured problem-solving activity.

All individuals with first-episode psychosis will participate in the MFG intervention for twelve months. This duration of treatment is consistent with recommendations from the Patient Outcomes Research Team (PORT) convened by the Agency for Health Care Policy and Research and the National Institute of Mental Health [39,40]. Of note, unlike the traditional MFG model, family groups in this study will be run using rolling admissions with families graduating from the group after twelve months of participation.

#### Cognitive Remediation

Individuals with first-episode psychosis who are randomized to the MFG and CR condition will complete the cognitive remediation program PSSCogRehab [41]. This computerized cognitive remediation program provides participants with training in 4 areas of cognitive functioning: attention, visual-spatial abilities, memory, and problem-solving abilities. Participants initially complete simple tasks in each domain and, once mastered, gradually progress to more difficult tasks. Completion of the training program occurs once subjects have mastered all of the training tasks. This program has been frequently used in past studies of cognitive remediation in psychotic disorders [42-48], and more recently has been applied specifically among individuals early in the course of a psychotic illness [49,50]. This intervention has been shown to promote improvements in problem-solving among individuals with psychotic disorders [42], and has been administered successfully with other concurrent psychosocial interventions [44].

### Primary Outcome Measure

#### Relapse

Symptomatology among individuals with first-episode psychosis will be assessed using the Positive and Negative Syndrome Scale (PANSS) [51] on a weekly basis during their participation in the study. Based on participants' scores on this measure, the occurrence of a relapse will be determined using the criteria established by Nuechterlein and colleagues [52]. Of note, although the criteria outlined by Nuechterlein and colleagues were designed for use with the Brief Psychiatric Rating Scale (BPRS [53]), the specific items on the BPRS used to determine the occurrence of a relapse using the Nuechterlein criteria (i.e., hallucinations, unusual thought content, and conceptual disorganization) are also included in the PANSS (i.e., hallucinations, delusions, and conceptual disorganization). These shared items are scored in an identical manner on both measures and each item on BPRS has been shown to be strongly correlated with its comparable item on the PANSS (weighed kappas of 0.65 [good] to 0.86 [excellent]) [54].

### Secondary Outcome Measures

Recognizing that recovery from psychotic disorders involves more than just a remission of psychotic symptoms [55], we will also explore the benefit of combining MFG and CR on other outcomes among individuals with first-episode psychosis. These will include social and vocational functioning (Social Functioning Scale: SFS [56]), everyday functioning (brief form of the UCSD Performance-Based Skills Assessment: UPSA [57]), health-related quality of life (RAND 36-Item Health Survey [58]), service utilization (Service Utilization and Resources Form for Schizophrenia: SURF [59]), and independent living status. Independent living status will be assessed using the methodology outlined by Palmer et al. [60]. Per this methodology, subjects' living status will be rated on a 4-point scale ranging from (1) 'totally dependent' (i.e., living in a facility with 24-hour clinical care) to (4) 'independent' (i.e., living alone or with a partner who provides a level of support consistent in typical cohabitation relationships). These measures will be administered when subjects enroll in the study and again after the completion of 12 months of MFG.

Additionally, to replicate findings linking participation in CR to improved cognitive functioning among individuals with psychotic disorders [26], individuals with first-episode will complete the consensus cognitive battery developed by the National Institute of Mental Health's Measurement and Treatment Research to Improve Cognition in Schizophrenia (MATRICS) initiative [61]. Of note, this battery does include a specific assessment of problem-solving skills (i.e., the mazes subtest from the Neuropsychological Assessment Battery [62]). Participants in the MFG and CR condition will complete the MATRICS battery three times over the course of the study: (i) at enrollment; (ii) upon completion of CR intervention, and (iii) upon completion of 12 months of the MFG intervention. Individuals randomized to the MFG alone condition will complete the MATRICS battery three times over the course of the study: (i) at enrollment, (ii) at 10 weeks, and (iii) upon completion of 12 months of the MFG intervention

Caregiving relatives of individuals with psychotic disorders have also been shown to experience a reduction in caregiver burden and psychological distress (e.g., depression and anxiety) after participation in family psychoeducation [63,64]. Thus, we plan to conduct additional secondary analyses to examine whether caregivers whose ill relatives are in the MFG and CR group experience greater benefits in these areas as compared to caregivers whose ill relatives are in the MFG alone condition. Caregiver burden will be assessed using the Burden Assessment Scale [BAS] [65], and depression and anxiety will be assessed using the Beck Depression Inventory [BDI] [66] and Beck Anxiety Inventory [BAI] [67], respectively. These measures will be administered upon enrollment to the study and after completion of 12 months of MFG.

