### Proposed Analyses

All analyses will be completed using an "intention-to-treat" principle [68] such that data from all subjects will be included in the analysis regardless of their level of adherence to the interventions over the course of the study.

The association between intervention condition (i.e., MFG and CR vs. MFG alone) and relapse will be examined using a chi-square. However, in situations in which the requirements for this analysis are violated (e.g., expected value of any cell ≤ 5), Fisher's exact probability test [69] with the continuity correction proposed by Overall [70] will be used instead.

Per the recommendations outlined by Vickers and Altman [71], the association between intervention condition (i.e., MFG and CR vs. MFG alone) and continuous secondary outcome measures (e.g., caregiver burden and social functioning scores) will be examined using an analysis of covariance with participants' baseline scores on the secondary outcome measure included as a covariate. With regard to the association between intervention condition and categorical secondary outcome measures (e.g., employed vs. unemployed), a chi-square analysis will be used. However, in situations in which the requirements for this analysis are violated, Fisher's exact probability test [69] with the continuity correction proposed by Overall [70] will be used instead.

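### Final secondary and caregiver assessments are tied to completing 12 months of MFG instead of to time since randomisation, which conflicts with the stated intention-to-treat principle

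*Protocol article*

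**What the plan says.** All references are to the protocol article.

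- **Secondary Outcome Measures, patients.** The Social Functioning Scale, brief UPSA, RAND-36, SURF and independent living status share one schedule: "These measures will be administered when subjects enroll in the study and again after the completion of 12 months of MFG".
- **Secondary Outcome Measures, MATRICS.** After enrolment, the MFG and cognitive remediation (CR) arm is tested "ii) upon completion of CR intervention, and (iii) upon completion of 12 months of the MFG intervention". The MFG-alone arm is tested "i) at enrollment, (ii) at 10 weeks, and (iii) upon completion of 12 months of the MFG intervention".
- **Secondary Outcome Measures, caregivers.** For burden, depression and anxiety: "These measures will be administered upon enrollment to the study and after completion of 12 months of MFG".
- **Proposed Analyses.** All analyses follow intention to treat, so that "data from all subjects will be included in the analysis regardless of their level of adherence to the interventions". Continuous secondary outcomes are compared by analysis of covariance with the baseline score as covariate.
- **Relapse.** The PANSS, from which the primary outcome is derived, is rated "on a weekly basis during their participation in the study".
- **Number of Participants and Power Analysis.** Six families are added to 34 to allow for attrition, giving 40.

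**The concern.** The event that triggers the final assessment is a treatment milestone. A patient who stops MFG at month 4 does not complete 12 months of it, and on the plain wording no final assessment falls due for that patient or for the caregiver. For the functioning and caregiver measures this is the only assessment after baseline, so the analysis of covariance has no outcome value for these people.

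The intention-to-treat statement covers all analyses and is there precisely so that poor adherence does not remove anyone. The schedule and the analysis principle therefore pull in opposite directions. If leaving is related both to arm and to how the person is doing, comparing only those who finish is biased. One arm carries an additional intervention, so unequal leaving is plausible, though nothing in the article shows it. An analysis plan can specify how missing values are handled, but it cannot recover assessments that were never scheduled.

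**Working it through.** **1. Which outcomes the wording touches**

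| Outcome | Trigger for the last assessment | Affected? |
|---|---|---|
| SFS, UPSA, RAND-36, SURF, living status | completion of 12 months of MFG | yes; only post-baseline score |
| Final MATRICS, both arms | completion of 12 months of MFG | yes |
| Caregiver burden, depression, anxiety | completion of 12 months of MFG | yes; only post-baseline score |
| MATRICS at 10 weeks, MFG alone | calendar time | no |
| Relapse (PANSS) | weekly during study participation | no |

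**2. How many people could be affected**

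The plan's attrition step reproduces: 34 + 6 = 40, with 6/40 = 15% and 34/(1 - 0.15) = 40. If all six left MFG and were not assessed, 34 of 40 patients would have final scores. At the expected 1.5 caregivers per patient (Sample Characteristics), that is 34 x 1.5 = 51 of 40 x 1.5 = 60 caregivers. These are upper bounds on the loss caused by the wording: anyone who leaves the study altogether stays missing under any schedule.

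**3. Precision**

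Assume two-sided alpha 0.05, power 0.80 and equal arms. The detectable difference in SD units is (1.960 + 0.842) x sqrt(2/n).

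- n = 17 per arm: 2.802 x sqrt(2/17) = 0.96 SD
- n = 20 per arm: 2.802 x sqrt(2/20) = 0.89 SD

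With an assumed baseline-to-final correlation of 0.5, multiply by sqrt(1 - 0.25) = 0.866, giving 0.83 and 0.77 SD. The loss of precision is modest.

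**4. Bias**

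Let d be the share of an arm that leaves and D the amount, in SD, by which leavers score worse than stayers. The arm mean is (stayers' mean) - d x D, so the stayers' mean overstates the arm mean by d x D. With no true effect, the contrast among stayers is off by (d2 - d1) x D. Take 20 per arm, six leavers in total, and D from 0.5 to 1.0 (assumed; the article gives no figure).

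| Leavers by arm | d1, d2 | Bias at D = 0.5 | Bias at D = 1.0 |
|---|---|---|---|
| 3 vs 3 | 0.15, 0.15 | 0 | 0 |
| 2 vs 4 | 0.10, 0.20 | 0.05 SD | 0.10 SD |
| 0 vs 6 | 0.00, 0.30 | 0.15 SD | 0.30 SD |

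These figures ignore the baseline covariate, which would reduce the bias to the extent that leaving tracks the baseline level.

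**The case against.** The strongest reply is that completing 12 months simply means reaching month 12. The Multifamily Group Psychoeducation section says "All individuals with first-episode psychosis will participate in the MFG intervention for twelve months" and sets no attendance threshold. On that reading a poor attender who stays enrolled is still assessed, and the schedule is compatible with the intention-to-treat statement. This is a possible reading, and it does cover poor attenders. It does not settle the case of people who stop MFG. The plan expects attrition, and the MATRICS schedule uses a calendar time where it means one (10 weeks in the MFG-alone arm). In the same schedule, completion for CR is a treatment event: "Completion of the training program occurs once subjects have mastered all of the training tasks". At best the wording is ambiguous.

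A second reply is that a condensed article leaves the follow-up of withdrawals to the full protocol or analysis plan. That is fair for missing-data methods, and their absence is not the point here. The article does state the schedule, and the point rests on what it states.

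Three stronger readings are tempting and not supported:

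- **That the intention-to-treat analysis as a whole cannot be done.** The primary outcome comes from weekly ratings during study participation, so a person who leaves treatment but stays in the study can still contribute. Nothing in the article says that PANSS ratings stop when MFG stops.
- **That the 12-month clock starts only after joining and the workshop, so follow-up time varies.** The article counts both as phases of MFG. Its remark that families graduate from the group after twelve months leaves the start of the clock unclear, but does not establish the later start.
- **That 34 instead of 40 patients is the effect of this wording.** It is the ceiling, as shown above.

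**Conclusion.** The point holds for the secondary outcomes only. The final patient and caregiver assessments are anchored to treatment completion, and taken literally this excludes the very people whom the intention-to-treat statement promises to include. The size depends on who leaves: no bias if leaving is balanced, a small bias at 2 vs 4, and up to 0.30 SD in the extreme case of 0 vs 6. These results rest on the budgeted six leavers and an assumed 0.5 to 1 SD deficit in leavers. Against a detectable difference of about 0.9 SD this is not dramatic, but the missing scores cannot be recovered after the event, and the correction is simple if made beforehand. The planned sample size and the primary test are unchanged.

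**What to change.** State that the final patient assessments (SFS, UPSA, RAND-36, SURF, living status, final MATRICS) and all final caregiver assessments take place 12 months after randomisation, within a fixed window, for everyone randomised and their caregivers who still consent to assessment, whether or not they still attend MFG or CR. Patients are randomised upon enrolment, so this also fixes the interval from baseline.

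The cost is a change of schedule wording and some effort to contact people who have stopped treatment. If the team counts the twelve months of MFG from a point after randomisation, some participants would be assessed shortly before they finish the group. Both arms receive MFG, so this should fall on them alike. No change to the weekly PANSS schedule is needed for this point.

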#### Number of Participants and Power Analysis

Current recommendations for a priori determination of the number of subjects to include in a study suggest the inclusion of sufficient subjects to maintain adequate statistical power to detect a clinically meaningful effect size [34]. One such measure, Number Needed to Treat (NNT) [35], has been identified as particularly useful in conveying clinical significance and in guiding the design of randomized clinical trials [36]. NNT provides an estimate of the number of individuals who would need to receive a treatment in order to prevent the occurrence of one negative outcome. With regard to family psychoeducation, a recent meta-analysis found that the NTT for this intervention was 8; (95% CI 6-18) [9]. This suggests that this intervention would need to be provided to 8 individuals to prevent one relapse. Although there is no established criteria for a clinically meaningful reduction in NNT [36], for the current study we defined a clinically meaningful benefit of the MFG and CR condition as an NNT one-half the size of the NNT for MFG along (i.e., an NNT for MFG and CR = 4). This value (i.e., NNT = 4) falls outside of the 95% confidence interval of the NNT for family psychoeducation alone as reported in a past meta-analysis [9] and is consistent with the NNT value use to determine a priori statistical power for most randomized controlled trials of interventions for mental illnesses [36]. Using these NNT values and the pwr software package [37] developed for the R statistical platform [38], we determined that 17 families (i.e., individual with first-episode psychosis and caregiving relative[s]) would need to be allocated to both the MFG-CR and MFG alone conditions, respectively, to ensure statistical power of 0.80 (i.e., total sample size = 34). To protect against subject attrition, we will recruit an additional 6 families (i.e., ≈20% of the total sample size), bringing the total sample size to 40.

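### The middle MATRICS battery is tied to finishing cognitive remediation in one arm and to week 10 in the other, so the arms are not compared on equal terms at that visit

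*Protocol article*

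**What the plan says.** Secondary Outcome Measures in the protocol article schedules the MATRICS battery three times in each arm. The first is at enrollment in both. For the MFG and CR arm the other two are "ii) upon completion of CR intervention, and (iii) upon completion of 12 months of the MFG intervention". For the MFG alone arm the full list is "i) at enrollment, (ii) at 10 weeks, and (iii) upon completion of 12 months of the MFG intervention". The first and third occasions match; the second does not.

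Cognitive Remediation describes a programme paced by performance: "Participants initially complete simple tasks in each domain and, once mastered, gradually progress to more difficult tasks". Its end point is defined the same way: "Completion of the training program occurs once subjects have mastered all of the training tasks". The article gives no expected length, no maximum length and no date for a middle battery in someone who does not finish.

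The battery's stated purpose is "to replicate findings linking participation in CR to improved cognitive functioning among individuals with psychotic disorders". Proposed Analyses commits to intention to treat, so that "data from all subjects will be included in the analysis regardless of their level of adherence to the interventions", and says that continuous secondary outcomes "will be examined using an analysis of covariance with participants' baseline scores on the secondary outcome measure included as a covariate". No term for assessment time is mentioned.

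**The concern.** One arm is tested when an event happens, the other on a date. This raises two separate problems for a between-arm comparison at the middle visit.

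- **Timing.** Time since enrollment, the test-retest interval and the amount of MFG received can differ between arms. Within the CR arm they vary with how fast a participant learns.
- **Selection.** The trigger for the CR-arm visit is mastery of tasks in attention, visual-spatial ability, memory and problem solving. That is a post-randomisation event plausibly related to what MATRICS measures. A participant who never masters all tasks never triggers the visit, while every control is scheduled for one.

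At stake is the only cognitive assessment placed at the end of CR. The Background section makes better problem solving the route by which CR should add to MFG, so a distorted result here would colour the reading of the mechanism.

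**Working it through.** The document gives no figure to reproduce on this point. The check is a reading of the sections against each other, followed by an illustration of scale.

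**Step 1: anchors of the three batteries.**

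| Battery | MFG and CR | MFG alone | Same anchor? |
|---|---|---|---|
| First | Enrollment | Enrollment | Yes |
| Second | Mastery of all CR tasks, no week stated | 10 weeks | No |
| Third | End of 12 months of MFG | End of 12 months of MFG | Yes |

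**Step 2: does the planned analysis repair the mismatch?** The ANCOVA adjusts for baseline score. It can absorb differences in starting ability. It cannot absorb a different retest interval or different MFG exposure, and it cannot supply scores that were never scheduled.

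**Step 3: timing effect.** This cannot be computed, because no CR duration or distribution of completion times is given. The sign is open too. A longer interval could reduce practice gain, which works against CR, or allow more recovery and more MFG, which works in its favour. A shorter interval would do the reverse.

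**Step 4: selection effect, for scale only.** Assume no true CR effect. Let q be the share of the CR arm reaching mastery, and r the correlation between an underlying normal liability to mastery and the baseline-adjusted cognitive score. Neither is in the document. If the top share q complete, the completers' mean exceeds the full-arm mean by

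bias = r × φ(z) / q, where z is the (1 − q) normal quantile, in SD units of the baseline-adjusted score.

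For q = 0.70, z = −0.524 and φ(z)/q = 0.50. Then 0.3 × 0.50 = 0.15 and 0.5 × 0.50 = 0.25.

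| Share completing (q) | r = 0.3 | r = 0.5 |
|---|---|---|
| 1.0 | 0 | 0 |
| 0.9 | 0.06 | 0.10 |
| 0.8 | 0.10 | 0.18 |
| 0.7 | 0.15 | 0.25 |
| 0.6 | 0.19 | 0.32 |

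All non-zero entries favour MFG and CR.

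**Step 5: set against sampling error.** With 40 recruited and equal allocation assumed, each arm has 20. At q = 0.7 the comparison is 14 against 20, with standard error √(1/14 + 1/20) = 0.35 SD. The illustrative bias at that completion rate is below one standard error.

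**The case against.** The strongest reply is that the plan already contains a sound comparison. The 12-month battery has the same anchor in both arms and does not depend on mastery. With the baseline-adjusted ANCOVA it gives an intention-to-treat test of cognition free of both problems. This stands, and it limits the point to the middle visit.

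A reader might infer that the middle battery is the trial's test of whether CR improves cognition. The article does not say so. It lists three occasions, names none as the main comparison, and does not state which post-baseline score enters the ANCOVA.

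A reader might also infer that the schedule flatly contradicts the intention-to-treat statement. That goes too far. The article is silent on participants who do not finish CR, and the full protocol may hold a fallback visit. What stands is that the schedule as printed has no middle score for them, which sits poorly with analysing everyone regardless of adherence.

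Ten weeks may be the expected length of CR. The article does not say this, and a match on average would still leave individual variation and unassessed non-completers.

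Testing at the end of training also has a legitimate use, since it shows what completed CR achieves. That supports keeping such a battery as description, but not using it for the randomised comparison.

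Finally, mastery may depend largely on baseline cognition, for which the ANCOVA adjusts, so the residual correlation could be small. This is fair, and it is one reason the figures are only illustrative.

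**Conclusion.** The mismatch is real and follows from the text. A between-arm MATRICS comparison at the middle visit cannot separate a CR effect from differences in retest interval and MFG exposure, and it leaves CR non-completers without a scheduled score.

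It would be tempting to say that the whole design leans toward CR. The documents do not support that: the timing effect has no known direction, and only the selection part has an arguable sign. That part runs from zero with full completion, through about 0.06 SD (90% completing, r = 0.3), to 0.15 to 0.25 SD (70% completing, r = 0.3 to 0.5). It rests wholly on assumed completion rates and correlations.

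The issue is moderate. It touches one intermediate time point of one secondary outcome. The 12-month cognitive comparison, relapse and the other secondary outcomes are unaffected.

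**What to change.** Give the middle MATRICS in one common window in both arms, 10 weeks after enrollment as already set for controls, whether or not CR is complete. Base between-arm cognitive comparisons on that visit and on the matched 12-month visit. Treat any battery given at CR completion as descriptive.

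The cost is a schedule amendment with no added required assessments. Some CR participants will be tested before they finish the programme, which may dilute the effect seen at that visit. If a completion battery is kept as well, it adds a retest in the CR arm only, and the extra practice should be borne in mind when the 12-month scores are read. The change is best made before data accrue, because scores not collected at a common time cannot be recovered by analysis.
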